#### Primary outcome

##### Submaximal aerobic exercise capacity

The primary outcome is changes in Watts (W) on the submaximal exercise test on a bicycle ergometer from baseline to the first follow-up visit (16 weeks). Blood pressure and heart rate are registered before the start of the test. The test is performed on a bicycle ergometer according to the WHO protocol [25], with an increased workload of 25 W every 4.5 min [26, 27]. The initial starting load, 25 W or 50 W, is decided, based on the patient’s exertion history. A pedalling rate of 50 rates per minute is used. After 2 and 4 min of each workload; heart rate, rating of perceived exertion according to Borg’s rating of perceived exertion scale (RPE) [28] and subjective symptoms, including chest pain and dyspnea according to Borg’s Category Ratio Scale, CR-10, scale are rated. After 3 min, the systolic blood pressure is registered. The exercise test is discontinued at Borg RPE 17 and/or dyspnea 7 on Borg’s CR-10 scale. The submaximal exercise test on a bicycle ergometer is a well-established, safe procedure that is frequently used in exercise-based CR in Sweden. The reliability of this test is currently being tested on a Swedish population with CAD.

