### Statistical methods

Data analysis will be performed using SPSS for Windows (IBM Corp. Armonk, NY). Descriptive statistics will be used for demographic data. The normally distributed continuous variables (ratio and interval data) will be presented as the mean ± 1SD. Skewed ratio and interval data, as well as ordinal data, will be presented as the median and 25th-75th percentiles. For nominal data (categorical variables), absolute and relative numbers (%) will be described.

Differences between groups will be tested with Student’s t-test for normally distributed ratios and interval data or the Mann-Whitney U test for skewed data. For comparisons of paired observations within each study group, a paired t-test (normally distributed) or Wilcoxon’s rank sum test (skewed data) will be used. For nominal data, differences within and between the groups will be calculated with a chi-square test. We will perform an-intention-to-treat and a per-protocol analysis. If adequate, missing data will be handled with multiple imputation. In addition, an analysis of predictors of rehabilitation outcomes will be calculated. A *p*-value of <0.05 will be considered statistically significant.

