### Sample size calculation

Sample size calculations are based on previous clinical data from a similar exercise-based CR setting (*n* = 50) for differences in aerobic exercise capacity measured by a submaximal exercise test (Watts) before and after completed exercise-based CR. With a power of 80% and a two-sided significance level of *p* < 0.0, a least mean difference at 10 W (SD 20 W) and a calculated loss of follow-up of 20%, the estimated total sample size is 160 patients.

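### The primary between-group test depends on whether change in Watts is judged skewed, and the Mann-Whitney branch does not estimate the 10 W mean difference the trial was sized on

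*Protocol article*

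**What the plan says.** All references are to the protocol article.

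- **What is measured:** "The primary outcome is changes in Watts (W) on the submaximal exercise test on a bicycle ergometer from baseline to the first follow-up visit", that is, at week 16 (stated under Submaximal aerobic exercise capacity). The test is staged, "with an increased workload of 25 W every 4.5 min". How an incomplete last stage is scored is not stated.
- **Test rule** (Statistical methods): continuous outcomes are compared between arms by t-test when normal, "or the Mann-Whitney U test for skewed data". The primary outcome has no rule of its own.
- **Summary measure** (same section): "Skewed ratio and interval data, as well as ordinal data, will be presented as the median and 25th-75th percentiles".
- **Sample size** (Sample size calculation): "a least mean difference at 10 W (SD 20 W", 80% power, two-sided, 20% loss to follow-up, 160 patients in total.
- **Setting** (Study design; Procedure): the trial is open-label, the testing physiotherapists know the allocation, and randomisation is stratified at 100 W of baseline submaximal capacity.

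**The concern.** The rule lets the observed outcome distribution decide what the primary analysis is. Its two branches answer different questions. The t-test compares mean change in Watts, which is the quantity behind the sample size. Mann-Whitney compares rank distributions, and the summary the plan attaches to it is the median. Neither the test nor the median estimates a mean difference of 10 W.

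Because *skewed* has no stated criterion, the choice is left to judgement after the data are in. The trial is open-label with unblinded testers, so the primary analysis is better closed to such judgement.

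The staged test makes the question practical. If the result is recorded as completed stages, change in Watts falls on multiples of 25 W with many ties. A median then moves in coarse jumps and is a poor description of a 10 W effect.

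**Working it through.** **1. The plan's own figure.** Inputs: difference 10 W, SD 20 W, power 80%, two-sided, loss 20%, equal allocation. Alpha is taken as 0.05 from Statistical methods ("<0.05 will be considered statistically significant"), because the value printed in Sample size calculation is cut short.

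Normal approximation: n per arm = 2 × SD² × (z₀.₉₇₅ + z₀.₈₀)² / Δ² = 2 × 400 × (1.960 + 0.842)² / 100 = 62.8, so 63. Total 126; 126 / 0.8 = 157.5, so 158.

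With the t distribution: 63.8, so 64 per arm. Total 128; 128 / 0.8 = 160.

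The stated 160 is reproduced exactly as a comparison of two means. With 64 completers per arm, power for 10 W is 80.1%.

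**2. How often the rule would switch.** The article gives neither the criterion nor the scoring of the last stage, so both were varied. Assumed model: baseline normal (mean 110, SD 35 W), change normal (mean 15 v 25, SD 20 W), both visits rounded down to the scoring step, 64 per arm, 3,000 trials. Each criterion counts as met if p<0.05 in either arm.

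| Scoring step | Shapiro-Wilk rejects | Skewness test rejects |
|---|---|---|
| 25 W (whole stages) | 100% | about 9% |
| 12.5 W (half stages) | 98% | about 9–10% |
| 5.6 W (per minute, 25/4.5) | about 21–22% | about 9% |
| 2.8 W (per half minute) | about 11–12% | about 10% |
| Unrounded | about 10% | about 10% |

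At 25 W, Shapiro-Wilk rejects because of the ties, not because of skew: absolute skewness exceeded 1 in either arm in only 0.3–0.4% of trials.

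**3. What the Mann-Whitney branch would report.** A second symmetric model draws normal change with SD √(400 − 625/12) = 18.7 W and rounds it to the nearest 25 W, giving a recorded SD of 19.9 W (4,000 trials). The mean difference averages 10.0 W. The difference in medians is 0 W in 77% of trials, 12.5 W in 7% and 25 W in 16%. The Hodges-Lehmann shift is 0 W in 75% and 25 W in 25%. Under the rounding-down model of step 2 the difference in medians is 0 W in 73%. Across symmetric whole-stage models the share is about 70–77%.

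With right-skewed change in 25 W steps (gamma shape 2, sample skewness about 1.2, realised mean difference 9.4 W), the difference in medians is 25 W in 71% and 0 W in 22%.

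**4. Error rates.** Switching rule with Shapiro-Wilk as trigger; 4,000 trials, 64 per arm.

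| Change in Watts | Type I error of rule | Power, t-test | Power, Mann-Whitney |
|---|---|---|---|
| Continuous normal | 4.6% | 79% | 77% |
| Symmetric, 25 W steps | 5.7% | 81% | 79% |
| Right-skewed, 25 W steps | 4.5% | 75% | 83% |

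Under the rounding-down model at 25 W, always taking the smaller of the two p-values gives a type I error of only about 6%. In that model power is about 70% for both tests. The loss from 80% comes from coarse scoring and is shared by both tests; the switching rule does not cause it.

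**The case against.** **Mann-Whitney as the likely branch.** A reader might infer this from the 25 W steps. The documents do not support it. The trigger word is *skewed*, no formal normality test is named, and stepped data need not be skewed. On symmetric stepped data a skewness test keeps the t-test in about nine trials out of ten. Whole-stage scoring is the plain reading of a staged test but is not stated, and per-minute credit brings even Shapiro-Wilk rejection down to about a fifth.

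**Damage to error rates.** A reader might also infer an inflated type I error or lost power. Neither appears, and under right skew Mann-Whitney is the stronger test. This objection stands in full.

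**Loss of the Watt estimate.** Choosing Mann-Whitney for the p-value does not forbid also reporting a mean difference with a confidence interval. That is correct. But the plan's stated summary for that branch is the median, and no other estimate is named.

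**Adjustment.** That Mann-Whitney takes no account of baseline or stratum is no argument against the switch, because the plan's plain t-test does not either.

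**Scope.** A condensed article may leave the skewness threshold to a fuller analysis plan. That covers the missing threshold. It does not cover the rule itself, which the article states and which, as written, includes the primary outcome.

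**Conclusion.** The point holds as a defect of estimand and pre-specification. The primary test is conditional on the data, the condition is undefined, and one branch does not estimate the quantity that gives 160 patients.

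The frequency of the switch cannot be fixed from the article. With symmetric underlying change it ranges from roughly 10–20% (skewness tested directly, or scoring per minute or finer) to almost always (formal normality test with whole- or half-stage scoring). Markedly right-skewed change would trigger the rule on its own terms, but nothing in the article shows that such skew is expected.

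In the whole-stage case a true 10 W mean effect would usually appear as a 0 W difference in medians. Type I error stays near 5%. Power differs by about 2 points in the symmetric cases and favours Mann-Whitney under skew.

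These sizes rest on assumed distributions, a control change of 15 W and assumed triggers, none of which the article gives. The conclusion is confined to the primary outcome; nothing here was shown for the other scores.

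**What to change.** State one primary analysis without a condition: the difference between arms in mean Watts at 16 weeks, from a linear model with baseline Watts and the 100 W randomisation stratum as covariates, reported with a 95% confidence interval. With baseline in the model, this is the same between-group contrast as for change in Watts. If residuals are clearly non-normal, use robust or bootstrap standard errors and keep the same estimate. Name Mann-Whitney as a sensitivity analysis, and keep medians for description.

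The cost is wording only, settled before outcomes are compared by arm. No extra data are needed, since baseline Watts and stratum are already collected. N stays 160: the 80.1% power with 64 completers per arm already refers to a comparison of means.

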#### Primary objective

The primary objective is to investigate the effect of a behavioural medicine intervention in exercise-based CR on submaximal aerobic exercise capacity, compared with usual care. (Sample size calculations are performed based on differences in submaximal aerobic exercise capacity at 16 weeks.)

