### Outcomes

Clinical and demographic patient characteristics are taken from medical records and patient interviews. Changes in the following variables will be measured from baseline to the first (16 weeks at end of intervention) and second (12 months after index event) follow-up visits.

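### The paired rank test is misnamed (rank sum instead of signed-rank) and one unspecified chi-square test covers both paired and independent nominal data; run as named, the affected within-group p-values are invalid

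*Protocol article*

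**What the plan says.** The relevant text is in the Statistical methods section of the protocol article.

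- Between arms, continuous data get Student's t-test if normal, "or the Mann-Whitney U test for skewed data".
- The within-arm sentence opens "For comparisons of paired observations within each study group" and continues: "a paired t-test (normally distributed) or Wilcoxon’s rank sum test (skewed data) will be used".
- For categorical data: "For nominal data, differences within and between the groups will be calculated with a chi-square test".
- The threshold is a p-value "<0.05 will be considered statistically significant", with no distinction between within-arm and between-arm tests.

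The data are paired because each patient is measured repeatedly. The Outcomes section states: "Changes in the following variables will be measured from baseline to the first (16 weeks at end of intervention) and second" follow-up visits. Neither the signed-rank test nor McNemar's test is named anywhere in the article.

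**The concern.** The rank sum test and the Mann-Whitney U test are the same procedure. As written, the plan therefore uses one independent-samples test for both the between-arm and the within-arm comparison of skewed data. Applied to two visits of the same patients, it treats 64 patients as 128 and ignores the correlation between visits.

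The chi-square wording has a related defect. The ordinary chi-square test of two proportions assumes independent groups, and nothing in the sentence says that the within-group version is different. An analyst could run it in two wrong ways: as a two-sample comparison of the visits, or on the cross-table of before by after. The second does not test change at all.

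At stake are the within-arm p-values for skewed or ordinal outcomes, and for any outcome analysed as categorical. HADS, the enablement and self-efficacy scores and the biomarkers could fall under the skewed-data rule.

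**Working it through.** **The plan's own figure.** Inputs from the Sample size calculation section: difference 10 W, SD 20 W, 80% power, two-sided, 20% loss. Alpha is taken as 0.05 from Statistical methods, because the sample-size sentence prints the level incompletely.

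n per arm = 2 × (1.96 + 0.842)² × (20/10)² = 62.8, so 63. The t-distribution version gives 64. Then 2 × 64 / 0.8 = 160, as stated. This leaves about 64 pairs per arm after loss.

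**Assumption.** The within-patient correlation ρ is not in the document. A range is shown.

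**Rank sum on paired data: formula.** Let the change SD be 20, so the true standard error of the mean change is 20/√64 = 2.5. A two-sample test assumes 2.5/√(1 − ρ). Approximately, on the normal scale:

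- actual type I error = 2 × [1 − Φ(1.96/√(1 − ρ))]
- power for a mean change of 10 = Φ(10/2.5 − 1.96/√(1 − ρ))

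Example at ρ = 0.5: 1.96/√0.5 = 2.77. Type I error is about 0.6%, and power is Φ(4 − 2.77) = 89%.

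**Simulation with the rank tests themselves** (bivariate normal data, 64 pairs, change SD 20):

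| ρ | Rank-sum type I error | Rank-sum power | Signed-rank power |
|---|---|---|---|
| 0 | about 5% | 97% | 97% |
| 0.3 | about 2% | 94% | 97% |
| 0.5 | about 1% | 87% | 97% |
| 0.7 | about 0% | 62% | 97% |
| 0.8 | about 0% | 33% | 97% |

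The formula gives 98%, 95%, 89%, 66% and 35% power, in line with the simulation. Signed-rank type I error stays near 5%.

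**Skewed data.** The disputed test is meant for skewed data, so the null check was repeated with lognormal values (64 pairs). Rank-sum type I error was 4.7%, 2.0%, 0.7%, 0.05% and 0% at ρ = 0, 0.3, 0.5, 0.7 and 0.9. Signed-rank stayed between 4.4% and 5.1%. For an illustrative shift of 0.3 SD on the log scale, power was 34% (rank sum) against 58% (signed-rank) at ρ = 0.5, and 29% against 79% at ρ = 0.7. At ρ = 0 the rank sum was slightly ahead, 38% against 33%.

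**Nominal data, no true change** (64 pairs, binary outcome from a latent normal scale with correlation ρ):

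| ρ | Two-sample chi-square rejects | McNemar rejects | Chi-square on before-by-after table rejects |
|---|---|---|---|
| 0 | 5.3% | 5.2% | 5.3% |
| 0.3 | 3.5% | 5.7% | 34% |
| 0.5 | 1.9% | 5.0% | 76% |
| 0.7 | 0.7% | 4.8% | 98% |

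The last column can be checked by hand. Take 30% positive at both visits in the margins and 22% positive at both in the same patients (assumed). Then φ = (0.22 − 0.09)/0.21 = 0.619, and the rejection rate is about Φ(√64 × 0.619 − 1.96) = Φ(2.99) = 99.9%, although nothing has changed.

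**The case against.** A naming slip is the likelier reading. The sentence is explicitly about paired observations, it puts the Wilcoxon test beside the paired t-test, and the preceding sentence already gives Mann-Whitney U to the between-arm case. Authors who meant the same independent-samples test would hardly name it twice in two ways. McNemar's statistic is also of chi-square type, so the generic wording does not strictly exclude it. No outcome listed in the protocol is defined as nominal, so the categorical figures above illustrate the method and not a specific planned analysis. The normal-data simulation borrows the sample-size SD, and normal data would go to the paired t-test; the lognormal check shows the same direction.

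These points stand, and they limit the weight of the finding. They do not make the text right. A slip in a named test is still a wrong instruction in the analysis plan, and nothing elsewhere corrects it. For nominal data, the same test is expressly shared between paired and independent comparisons.

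A reader might infer more: that every within-group p-value will be wrong, or that the trial's efficacy conclusion is at risk. The document does not support either. The first holds only if the tests are run literally, the normally distributed outcomes have the correct paired t-test, and the rank-sum error disappears as the correlation approaches zero. The second fails because the objective is the effect "on submaximal aerobic exercise capacity, compared with usual care", and the tests named for that comparison are valid for independent arms.

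**Conclusion.** Wrong as written, of minor to moderate weight. The rank sum test is the wrong named test for paired skewed data, and the paired nominal test is not identified.

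The consequence is conditional on literal use. With positive within-patient correlation, the rank sum test and the two-sample chi-square test are conservative, so real within-arm changes would be missed. The loss is small at a correlation of 0.3 and large at 0.7 or above. The exception is chi-square on the before-by-after table, which errs in the opposite direction and would report change where there is none. These sizes rest on assumed correlations, 64 pairs per arm and illustrative effects.

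The fault is confined to within-group comparisons, which are secondary to the stated objectives. The between-group tests, the primary outcome comparison and the total of 160 patients are not affected.

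**What to change.** In Statistical methods:

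- Replace Wilcoxon's rank sum test with the Wilcoxon signed-rank test for paired skewed data.
- For within-group nominal changes, name McNemar's test, or McNemar-Bowker for more than two categories.
- Restrict the chi-square test to between-group comparisons.

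In the simulations, the paired tests bring type I error back to about 5% (4.4% to 5.8% across all settings). The cost is a few words: no change to data collection, sample size or any between-group analysis.

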### Sample size calculation

Sample size calculations are based on previous clinical data from a similar exercise-based CR setting (*n* = 50) for differences in aerobic exercise capacity measured by a submaximal exercise test (Watts) before and after completed exercise-based CR. With a power of 80% and a two-sided significance level of *p* < 0.0, a least mean difference at 10 W (SD 20 W) and a calculated loss of follow-up of 20%, the estimated total sample size is 160 patients.

### Study status

The study started to recruit participants in January 2016. By March 2017, 71 patients had been included. Study inclusion is expected to be completed by 2018 and the completion of the second follow-up period is anticipated in 2019.

## Discussion

This is the first study to investigate the effects of a behavioural medicine intervention in physiotherapy, containing goal-setting, self-monitoring and feedback, on improvements in rehabilitation outcomes for exercise-based CR, compared with usual care. Despite the positive effects of exercise-based CR, adherence is sub-optimal in many countries [12, 14]. Given the stepwise benefits of greater programme participation, patients should not only be referred to and attend programmes, they should also participate as regularly as possible, according to international guidelines [4], to achieve the best possible health benefits [45].

One strength of the present study is that the behavioural medicine intervention that is used is grounded in a theoretical framework that is evidence based in other patient groups [46, 47]. The intervention is expected to be possible to implement in the existing exercise-based CR models. Another strength of the study is the long-term follow-up, making it possible to analyse the sustained effects of the behavioural change supporting intervention over time.

The limitations of the study include the single-centre design, which may affect the generalisability of the results. Moreover, because of organisational factors, it is not possible to blind the physiotherapists performing the tests to group allocation. However, the test protocols are standardised and the test procedure is validated between the physiotherapists that are involved. Another challenge in the study might be that the patients in the usual care group and the intervention group participate in the same exercise-based CR sessions at hospital. The physiotherapists that are involved are, however, strictly informed not to give any information about the behavioural medicine intervention during these exercise sessions.

To conclude, this paper presents the protocol and data analysis plan for an open-label, single-centre, randomised clinical study evaluating the role of an integrated behavioural medicine intervention in exercise-based CR in the effects of rehabilitation outcomes. When completed, the results of this study will provide valuable information about the effect of these interventions in exercise-based CR and it has the potential to inform and assist in further treatment in secondary prevention for patients with CAD.

## Abbreviations

CAD: Coronary artery disease
CCU: Coronay Care Unit
CR: Cardiac rehabilitation
CT: Control theory
HADS: Hospital Anxiety and Depression Scale
HRQoL: Health-related quality of life
PEI: Patient Enablement Instrument
SEE: Self Efficacy Scale for Exercise
VAS: Visual analogue scale
